**Methods:**

The AIM trial is a prospective, three-armed, phase II randomized controlled trial investigating the effects of a 16-week supervised circuit aerobic and resistance exercise (CARE) program versus a traditional aerobic and resistance exercise (TARE) program and attention control (AC) on adipose tissue inflammation in breast cancer survivors. 276 patients who are diagnosed with stage 0-III breast cancer, post-treatment, sedentary, and centrally obese are randomized to one of the three groups. The CARE and TARE groups participate in thrice-weekly supervised exercise sessions for 16 weeks. The AC group are offered the CARE program after the intervention period. The primary endpoint is adipose tissue inflammation assessed by core biopsy and blood draw. The secondary and tertiary endpoints are sarcopenic obesity, physical fitness and function, and patient reported outcomes. The exploratory outcomes are long-term breast cancer outcomes.

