• Over 18 years of age • Newly diagnosed women with stage 0-III breast cancer, low grade disease positive for estrogen and progesterone receptors • Having undergone lumpectomy or mastectomy, (neo)adjuvant chemotherapy and/or radiation therapy • Not receiving concurrent cancer treatment • Centrally obese with the following criteria: BMI >30 kg/m^2^ or body fat >30% (as measured by bioimpedance analysis), waist circumference >35 inches • Currently participating in less than 60 minutes of structured exercise per week • Without any cardiovascular, respiratory, or musculoskeletal disease or joint problems that preclude exercise • Not currently or planning to become pregnant • Speaking English	• Metastatic disease or other active malignancies • Currently receiving any other investigational agents, or concurrent biological, chemotherapy, or radiation therapy • Not completed any of breast cancer treatment (e.g., surgery, chemotherapy, or radiation) • Having uncontrolled illness including ongoing or active infection, uncontrolled diabetes, hypertension, or thyroid disease that preclude participation in exercise • Participates in more than 60 minutes of structured exercise/week • Is planning reconstructive surgery with flap repair during trial and follow-up period • Smoker • Unable to travel to research facilities

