#### 2.5.2 Secondary Outcomes

##### 2.5.2.1 Sarcopenic Obesity and Body Composition

Sarcopenic obesity is determined by body composition measured by dual-energy X-ray absorptiometry (DXA; *Hologic Inc., Marlborough, MA*). Appendicular fat-free mass (AFFM) is measured from a whole-body, hip, and spine scan, and predicted AFFM is calculated using the following equation: -14,529 + (17,989 * height in meter) + (0.1307 * total fat mass in kilograms) (33). A residual value of ≤-3.4 is defined as an individual having sarcopenic obesity (33). Lean mass, fat mass, and body fat % are also obtained from the whole-body DXA scan. A constant-tension tape measure is used to obtain waist circumference, defined as the distance around the waist using the umbilicus as the reference point, and hip circumference, defined as the distance around the widest girth of the buttocks using the greater trochanter as a landmark. Body composition is also assessed *via* bioelectrical impedance using a validated device (*Tanita 780, Arlington Heights, IL*) (34). The device estimates body fat using an algorithm based on their age, sex, height, and body weight.

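### The equation that defines sarcopenic obesity is printed with commas in two coefficients and decimal points elsewhere; taken literally, it would classify every woman as a case at every visit

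*Protocol article*

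**What the plan says.** Sarcopenic obesity is listed under Section 2.5.2, Secondary Outcomes, and Section 2.5.2.1 defines it in three steps.

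- Measurement by DXA: "Appendicular fat-free mass (AFFM) is measured from a whole-body, hip, and spine scan".
- A predicted AFFM from height and total fat mass. The intercept has a minus sign, and the rest reads "14,529 + (17,989 * height in meter) + (0.1307 * total fat mass in kilograms".
- A decision rule: "A residual value of ≤-3.4 is defined as an individual having sarcopenic obesity".

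The section prints no unit for AFFM or for the residual, and it does not say in which direction the residual is taken. It cites reference 33 for both the equation and the cut-off. The equation is not repeated or corrected anywhere else in the article. The abstract gives one joint list: "The secondary and tertiary endpoints are sarcopenic obesity, physical fitness and function, and patient reported outcomes". The Introduction hypothesises that CARE improves the secondary and tertiary outcomes more than TARE or attention control does.

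**The concern.** One short definition uses two number formats. The fat coefficient ("0.1307 * total fat mass in kilograms") and the cut-off of -3.4 use a point as the decimal mark, so a reader takes the commas in 14,529 and 17,989 as thousands separators. Loss of decimal points when the PDF was read is possible but unlikely, because points survive in the same two sentences and elsewhere (0.98 in Section 2.5.3.5, 91.4 cm in Section 2.5.3.6).

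This equation is the working definition of a secondary outcome. Coded literally, the classification would be constant across women, visits and arms. A programmer who noticed the size of the result and treated it as grams would get values that look plausible but are still wrong, and that error is harder to detect.

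**Working it through.** **Inputs from Section 2.5.2.1.** Intercept -14,529; height coefficient 17,989 per metre; fat coefficient 0.1307 per kg; cut-off -3.4.

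**Assumptions, not in the article.** The eligibility criteria describe the population ("BMI >30 kg/m^2^ or body fat >30% (as measured by bioimpedance analysis), waist circumference >35 inches") but give no heights or fat masses. I take height 1.50-1.75 m, fat mass 25-50 kg and measured AFFM 12-28 kg, with an example woman of 1.62 m and 38 kg fat. AFFM is in kg and residual = measured minus predicted; fat mass in kilograms and a negative cut-off for low muscle imply both. The article gives no worked value to reproduce.

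**1. Commas as thousands separators.**
- Example: -14,529 + 17,989 × 1.62 + 0.1307 × 38 = -14,529 + 29,142.18 + 4.97 = 14,618.
- Lowest: -14,529 + 17,989 × 1.50 + 0.1307 × 25 = 12,457.8.
- Highest: -14,529 + 17,989 × 1.75 + 0.1307 × 50 = 16,958.3.
- Residuals: from 28 - 12,457.8 = -12,429.8 to 12 - 16,958.3 = -16,946.3. All lie far below -3.4.
- The assumed ranges do not drive this. With 35 kg fat, the prediction reaches zero only at (14,529 - 4.57) / 17,989 = 0.81 m.

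**2. Output read as grams, fat mass still in kg.**
- Example: 14,618 g = 14.62 kg. The fat term adds 0.1307 × 38 = 4.97 g, so the adjustment for fat mass all but disappears.
- Shortfall against the decimal reading: 0.1307 × F - 0.0001307 × F = 0.13057 × F kg. This is 3.26 kg at F = 25 and 6.53 kg at F = 50, about as large as the 3.4 cut-off or larger.
- The cut-off of -3.4 would also have to change unit. The grams form is coherent only if fat mass is entered in grams and the cut-off becomes -3,400. The article says kilograms and -3.4.

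**3. Commas as decimal marks.**
- Example: -14.529 + 17.989 × 1.62 + 0.1307 × 38 = -14.529 + 29.142 + 4.967 = 19.58 kg.
- Lowest: -14.529 + 26.984 + 3.268 = 15.72 kg. Highest: -14.529 + 31.481 + 6.535 = 23.49 kg.
- At 1.62 m and 35 kg fat the prediction is 19.19 kg. Measured AFFM of 12, 16, 18 and 20 kg gives residuals of -7.19, -3.19, -1.19 and +0.81, so the cut-off separates women.

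**Threshold for a case, example woman.**

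| Reading | Case if AFFM is at or below |
|---|---|
| Decimal marks, cut 3.4 kg | 19.58 - 3.4 = 16.18 kg |
| Grams, cut 3.4 g | 14,618.1 - 3.4 = 14,614.7 g = 14.61 kg |
| Grams, cut 3.4 kg | 14.62 - 3.4 = 11.22 kg |
| Thousands | all women |

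For this woman both grams versions miss cases that the decimal version finds. With a 3.4 g cut the direction depends on fat mass: the thresholds cross at about 3.4 / 0.1307 = 26 kg, and below that the grams version classifies more women as cases.

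**The case against.** The strongest reply is that this is a misprint with one sensible reading. Reading the commas as decimal marks changes no digit and gives credible kilogram values. The source is cited at the same place, and an analyst who coded the line literally would see a predicted limb mass near 14,600 kg on the first record. Nothing in the article shows that the derivation code contains the error. All of this stands, and it lowers the severity. It does not remove the point, because the printed line is the definition of the outcome and cannot be applied as it stands.

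Three stronger readings are tempting, and the article does not support them.

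- *No treatment effect on sarcopenic obesity could be estimated.* This is true only of the binary classification. With height fixed, the change in a woman's residual is (change in AFFM) - 0.1307 × (change in fat mass) under both the thousands and the decimal reading, so a continuous residual would still carry information. DXA lean mass, fat mass and body fat % do not use the equation.
- *Sarcopenic obesity is the only endpoint that the abstract calls secondary.* The abstract pools secondary and tertiary endpoints. The secondary label comes from the Section 2.5.2 heading, and the subsection beneath it also covers body composition.
- *A grams reading always misses cases.* With a cut of 3.4 g, this reverses below about 26 kg fat.

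**Conclusion.** The point holds as a should-fix error in the printed definition of a secondary outcome. Read literally, the equation predicts about 12,500 to 17,000 over the assumed heights and fat masses and makes every woman a case at every visit, so the binary outcome could not differ between arms. That conclusion needs AFFM in kg and residual = measured minus predicted, which are implied but not printed; it is insensitive to the heights and fat masses chosen. Of the readings tried, only decimal marks agree with both the fat term in kilograms and the -3.4 cut-off.

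A reader might infer that the trial will report 100% prevalence or that its analysis is already wrong. The article does not show that. The primary outcomes, the continuous DXA measures and the sample size are unaffected.

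**What to change.** After checking the coefficients and the cut-off against reference 33, replace the equation in Section 2.5.2.1 with: predicted AFFM (kg) = -14.529 + 17.989 × height (m) + 0.1307 × total fat mass (kg). State that the residual is measured minus predicted AFFM in kg and that the -3.4 cut-off is in kg.

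Check the derivation code on one worked example: 1.62 m and 38 kg fat should return 19.58 kg, so a woman with those values is a case at a measured AFFM of 16.18 kg or less.

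The cost is a corrected line, a sentence on units and sign, and a short code check. No visit, measurement or sample size changes.

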#### 2.5.3 Tertiary Outcomes

##### 2.5.3.1 Cardiorespiratory Fitness

Cardiorespiratory fitness is assessed as VO_2peak_ during exercise exertion testing on a treadmill using the modified Bruce protocol (35). The test begins with a 5-minute warm-up, and a speed and incline increase every three minutes, concluding when the participant reached physical exhaustion and is unable to continue on the treadmill. A metabolic cart (*TrueOne 2400, ParvoMedic Inc., Salt Lake City, UT*) is used to measure gas exchange during the test, and VO_2peak_ is determined as the highest O_2_ value obtained at the maximal exertion. Heart rate (*Polar USA, Lake Success, NY*) and rating of perceived exertion (Borg CR10 scale) (36) are measured during the test. Results from this test are used to prescribe the target AE intensity. The 6-minute walk test is also conducted to assess aerobic endurance and capacity, which has been validated and widely used in cancer survivors (37, 38). Participants are instructed to walk as quickly as possible without running on an indoor pre-measured walkway for six minutes. Distance achieved during the 6-minute walk test is recorded in meters.

##### 2.5.3.2 Muscular Strength

Muscular strength is measured using one-RM. One-RM values are calculated and estimated from 10-RM using validated equations (39, 40). The test is conducted on a total of six exercises that are included in the intervention: 1) leg press, 2) leg extension, 3) leg curl, 4) chest press, 5) seated row, and 6) seated shoulder press (*Matrix Fitness, Cottage Grove, WI*). Following a warm-up, 3 attempts are given to reach the final 10-RM load with a 2-minute rest period between attempts. Grip strength is also assessed using a hand-held dynamometer on the participant’s dominant hand (*Camry Digital Hand Dynamometer, El Monte, CA*). In a standing position, participants grip the dynamometer handle with their arms down. Participants complete the test three times with the highest result recorded for analysis.

##### 2.5.3.3 Physical Function

Lower extremity physical function is assessed using the Short Physical Performance Battery (SPPB), which has been widely used and validated within the breast cancer population (41). This battery included three sections: 1) Timed balance is assessed with both feet side-by-side, semi tandem, and full tandem. These positions are held for 10 seconds with no external support or when the participant steps out of position. Participants have one attempt to complete the test, and the time in each position is recorded in seconds. 2) Gait speed is assessed over a 4-meter distance. Participant has two attempts and is asked to walk at their “usual” pace with the fastest time recorded in seconds. 3) Chair stand is assessed by recording the time in seconds that the participants need to complete five chair stands with only one attempt after a familiarization practice to ensure proper technique. Each section of the SBBP is given a score based on performance to then provide a total score.

Mobility and immediate fall risk are assessed using the Timed Up and Go (TUG) test (42). Participants start and end in a seated position assessing the time needed to walk around a cone placed 3 meters away, with three attempts to complete the test and one familiarization practice. The final time recorded in seconds is the average of the three attempts.

Gait speed is also assessed over a 6-meter flat surface. The time in seconds to walk the 6-meter surface at the participant’s “usual” and “fast” pace is recorded (43).

Functional power is measured using the Margaria Stair Climb test that has been previously used and associated with lower-extremity power and mobility in older adults (44). Participants walk/run up 10 stairs as fast, and safely, as possible. The time in seconds that the participant takes from the 3^rd^ stair to the 9^th^ stair is recorded, with three attempts given and a familiarization practice, where the average time is recorded.

Lastly, the sit-to-stand test is performed, with participants completing as many sit-to-stands as possible in 30 seconds. Participants are asked to rise to a full standing position. Only one attempt is given, and the number of total repetitions completed with the proper technique is recorded.

##### 2.5.3.4 Musculoskeletal Disorders

Peripheral neuropathy is assessed using two different tests (45–47). First, the Semmes-Weinstein Monofilament Examination (SWME), where participants are seated in an upright position with their socks and shoes removed and eyes closed. The SWME evaluates protective sensation at the pad of the great toe (foot), and at the pad of the index finger (hand). A nylon monofilament will be used and applied four times in each site. Second, vibration sensation is assessed by applying a tuning fork to the bony prominences of the great toe, thumb, and medial malleolus where the participant will verbally identify if the vibration stopped. The correct identification of the side of the body where the nylon monofilament was applied, and on/off vibration identification will be recorded.

##### 2.5.3.5 Lymphedema

Geometric arm volume calculations are performed to assess lymphedema on both upper limbs (48). We calculate arm volume using circumferential measurements taken at anatomic landmarks (48). The anatomic landmarks include the axillary fold, halfway between the axillary fold and antecubital fossa, antecubital fossa, halfway between antecubital fossa and wrist, and wrist. This method was determined to be a reliable and valid method of limb volume measurement. The participant will be supine, circumferential measurements will be taken with a constant tension tape measure. Calculations for limb geometric volume are completed using the frustum (truncated cone) volume (48). The interrater reliability for this method is high at >0.98 (49). We will calculate a percentage difference between the lymphedema limb and the uninvolved limb to examine the amount of lymphedema. Lymphedema is defined as a greater than 10% difference in volume calculation for the arm compared to the uninvolved upper extremity (48).

##### 2.5.3.6 Shoulder Range of Motion and Function

Shoulder active range of motion (AROM) is measured on both upper limbs. AROM is assessed in external rotation at 0°, external rotation at 90°, forward flexion, and abduction (50, 51), using a goniometer (*Jamar E-Z Read, Patterson Medical, Warrenville, IL*). Participants are standing in all tests except for external rotation at 90° where the participant is lying supine on the ground. Participants are asked to actively perform the movement tested. Participants perform the test three times after a familiarization trial where the tester passively moves the participant’s limb. The average of the three attempts is recorded in degrees.

The Y Balance Test Kit (*Move2Perform, Evansville, IN*) is used to assess upper body function (52). Starting position for the test is in a three-point plank on toes or knees depending on ability. The upper limb that is tested is placed on the main block and the non-tested limb is placed on the medial block. Feet are placed shoulder-width apart. Then, participants use their non-tested limb to move each block one at a time in the medial, inferolateral, and superolateral directions. The block must be moved in a controlled manner as far as possible, returning to the starting position once each block has been moved. Participants have three trials on each upper limb with 30 seconds rest between trials. The highest value obtained in each direction is used to calculate an average composite score.

Upper body strength and power are measured using the seated medicine ball throw (SMBT) (53). The starting position for this test is sitting on the floor with head, shoulders, and back against the wall and legs extended or bent depending on ability. The 2 kg medicine ball is held with both hands and covered in chalk. A measuring tape will be placed on the floor and stretched out over 10 meters. Participants will throw the medicine ball forward, in a straight line, as far as possible with head, shoulders, and back maintaining full contact with the wall. Participants have three trials and one familiarization trial with 60 seconds rest between each trial. To calculate a relative throwing distance, arm reach distance is measured from the wall in meters and then subsequently deducted from the total throwing distance. The average of the throwing distances is recorded in meters.

We assess upper body function using the closed kinetic chain upper extremity stability test (CKCUEST) (54). Starting position for the test is in a three-point plank on toes or knees depending on ability with hands 91.4 cm (36 in.) apart (marked with two stripes of tape on the floor) and with both shoulders perpendicular to their hands and feet hip-width apart. Participants use their dominant hand to reach across the body, touch the non-dominant hand, and return to the starting position. Then, they perform the movement with the non-dominant hand. Participants are asked to perform as many alternating touches as possible for 15 seconds. Participants have three trials and one familiarization trial with 45 seconds rest between each trial. The average repetitions of the three attempts are recorded.

Shoulder function is assessed through the shoulder performance test (SPT). Participants are asked to start in a standing position with arm by side and to perform the following task: overhead reach, hand behind the head, and hand behind the back. We record the time in seconds taken to complete 20 repetitions of each task. Participants have one attempt with both upper limbs.

Furthermore, upper limb musculoskeletal disorders will be assessed using the Disabilities of the Arm, Shoulder, and Hand (DASH), which is comprised of a 30-item questionnaire designed to measure physical function and musculoskeletal disorders symptoms (55).

##### 2.5.3.7 Cognition

The Montreal Cognitive Assessment is used to assess global cognition and the NIH toolbox (www.nihtoolbox.org) is used to measure executive abilities, including response inhibition, cognitive flexibility, working memory, planning, insight, social cognition and behavior, and verbal fluency. This toolbox includes the Auditory Verbal Learning Test for immediate recall, Picture Sequence Memory Test for episodic memory, Oral Reading Recognition for Language, the Flanker for executive function and attention, the List Sorting test for working memory, Oral Symbol Digit Test for processing speed, Dimensional Change Card Sort Test for executive function, and Pattern Comparison for processing speed. We include an episodic memory composite that is derived from tests supported by the hippocampus and surrounding medial temporal lobe (56). This battery also includes memory tasks, Logical Reasoning, and Visual Reproductions.

##### 2.5.3.8 Patient-Reported Outcomes

We assess various aspects of psychosocial outcomes using questionnaires that have been validated and used in breast cancer patients, including the Functional Assessment of Cancer Therapy-Breast (FACT-B) for breast cancer-specific health-related quality of life (57), the Brief Fatigue Inventory (BFI) for the severity and impact of cancer-related fatigue (58), the Brief Pain Inventory (BPI) for a sensory and reactive dimension (59, 60), the Center for Epidemiologic Studies Depression scale (CES-D) for depression, the Pittsburg Sleep Quality Index (PSQI) for sleep quality (61, 62), and the State-Trait Anxiety Inventory (STAI) for anxiety (63). Recruitment and exercise adherence barriers and participants’ burden to the intervention are assessed using the Barriers to Recruitment Participation Questionnaire (BRPQ) (64), the Exercise Benefits/Barriers Scale (EBBS) (64, 65),, and the Perceived Research Burden Assessment (PRBA) (66), respectively.

##### 2.5.3.9 Physical Activity and Sedentary Behavior

Physical activity and sedentary behavior are assessed using the ActiGraph wGT3X-BT (*ActiGraph LLC, Pensacola, FL*) at all assessment timepoints. Participants are asked to wear the accelerometer on their hip for 7 consecutive days, except when showering or swimming. Wake wear time is used with a minimal data collection period of 4 days of at least 600 minutes per day for inclusion. We exclude non-wear time from the analyses, considering those accelerometer data where ≥90 minutes of consecutive zeros with a 2-minute spike tolerance (67). We use cutoff points that are commonly used among cancer survivors: sedentary time (<100 counts per minute), light physical activity (100–1951 counts per minute), and moderate-to-vigorous physical activity (≥1952 counts per minute) (68–70). ActiGraph data is analyzed using ActiLife software (*ActiLife 6; ActiGraph LLC*).

#### 2.5.4 Exploratory Outcomes

##### 2.5.4.1 Breast Cancer Outcomes

Breast cancer events are commonly used in lifestyle trials (71–75). Disease-free survival (DFS) is defined as the time from randomization to the documentation of the first of any of the following events: invasive ipsilateral breast tumor recurrence; local, regional, distant recurrence; invasive contralateral breast cancer; or ipsilateral and contralateral ductal carcinoma in situ, second primary invasive cancer (excluding carcinoma *in situ* and skin cancer other than melanoma). Overall survival (OS), distant DFS (DDFS), and recurrence-free interval (RFI) are included as exploratory endpoints. OS is defined as the time from randomization to death from any cause. DDFS is defined as events that are either lethal (death from any cause) or a direct threat to patient survival (distant recurrence or second primary invasive cancer). RFI is defined as events directly attributable to the original breast cancer including invasive ipsilateral breast tumor recurrence; local, regional, or distant recurrence; and death from breast cancer. These efficacy end points are assessed by reviewing medical records annually for 8 years from the time the participant enrolls in the study. Participants are called by phone to confirm their disease status or to assess their disease status if their medical records are unavailable.

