### 2.6 Follow-Up Assessments

After the 16-week intervention, participants in the TARE and CARE groups will return 4 and 8 months after the post-intervention assessments to repeat the outcome measure testing. Medical record abstraction will occur for 8 years thereafter to assess prognostic outcomes (i.e. OS, DFS, etc.). During the follow-up period, participants will be encouraged to exercise independently, without study team supervision/intervention.

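### The DFS event list omits death, which OS and distant DFS count, so the exploratory breast cancer endpoints do not nest

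*Protocol article*

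**What the plan says.** Section 2.5.4.1 defines four long-term endpoints.

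- **DFS:** "Disease-free survival (DFS) is defined as the time from randomization to the documentation of the first of any of the following events". The list opens with "invasive ipsilateral breast tumor recurrence; local, regional, distant recurrence; invasive contralateral breast cancer" and closes with "or ipsilateral and contralateral ductal carcinoma in situ, second primary invasive cancer (excluding" in-situ carcinoma and skin cancers other than melanoma. No form of death appears.
- **OS:** time from randomization to death, whatever the cause.
- **DDFS:** "DDFS is defined as events that are either lethal (death from any cause) or a direct threat to patient survival", the latter being distant recurrence or a second primary invasive cancer.
- **RFI:** events attributable to the original cancer, including "local, regional, or distant recurrence; and death from breast cancer".

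No other section adds death to DFS. Section 2.6 only names DFS and OS as prognostic outcomes to be abstracted from records.

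On follow-up, Section 2.5.4.1 speaks of "reviewing medical records annually for 8 years from the time the participant enrolls in the study". Section 2.6, directly after describing the visits 4 and 8 months after the post-intervention assessment, says "Medical record abstraction will occur for 8 years thereafter to assess prognostic outcomes".

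**The concern.** DFS is the only one of the four endpoints that counts no death. By its name it should be the broadest, with DDFS as its distant-disease counterpart. As written, DDFS contains an event type that DFS lacks, so the two cannot be read as a broad endpoint and a narrower one inside it. The same holds for RFI: a breast cancer death with no documented recurrence is an RFI event but not a DFS event. That can happen here, because DFS is timed to documentation, records are reviewed once a year, and the fallback is a telephone call to the participant.

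At stake is the interpretation of the long-term results. The Introduction motivates the trial partly by the higher all-cause mortality that goes with obesity. An endpoint labelled survival that counts no deaths would not register an effect of the programmes on death before recurrence, in either direction.

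**Working it through.** The article gives no DFS event count, rate or power, so there is no stated figure to reproduce. The check is a comparison of event sets, followed by an illustration of size.

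**1. Event sets (Section 2.5.4.1), taking second primary invasive cancer to mean the same in DFS and DDFS**

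| Event | DFS | DDFS | RFI | OS |
|---|---|---|---|---|
| Invasive ipsilateral recurrence | yes | no | yes | no |
| Local or regional recurrence | yes | no | yes | no |
| Distant recurrence | yes | yes | yes | no |
| Invasive contralateral cancer | yes | no | no | no |
| Ductal carcinoma in situ, either side | yes | no | no | no |
| Second primary invasive cancer | yes | yes | no | no |
| Death from breast cancer | **no** | yes | yes | yes |
| Death from another cause | **no** | yes | no | yes |

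In DDFS but not in DFS: death from any cause. In RFI but not in DFS: death from breast cancer.

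**2. What follows for one woman**

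Suppose she dies 3 years after randomization with no listed DFS event before then. Her OS and DDFS both end with an event at 3 years. She has no DFS event at 3 years or at any later time, so her DFS has not ended when her DDFS has.

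**3. After adding death from any cause to DFS**

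Both death rows become yes for DFS. Every event in DDFS, RFI and OS is then also a DFS event, so DFS can never exceed any of them.

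**4. Illustration of size**

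Inputs: 276 women (Section 2.8) and 8 years (Section 2.5.4.1). The yearly rate r of death without a prior DFS event is assumed, with a constant hazard and complete follow-up.

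Deaths not counted = 276 × (1 − exp(−8r)):

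- r = 0.003: 276 × (1 − exp(−0.024)) = 6.5
- r = 0.005: 276 × (1 − exp(−0.040)) = 10.8
- r = 0.010: 276 × (1 − exp(−0.080)) = 21.2

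This ignores women who already had a DFS event. With an assumed rate e for the listed DFS events, uncounted first-event deaths = 276 × r/(r+e) × (1 − exp(−8(r+e))), and counted DFS events are the same expression with e in the numerator:

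| r | e | Uncounted deaths | Counted DFS events |
|---|---|---|---|
| 0.0025 | 0.01 | 5.3 | 21.0 |
| 0.0025 | 0.02 | 5.1 | 40.4 |
| 0.005 | 0.01 | 10.4 | 20.8 |
| 0.005 | 0.02 | 10.0 | 40.0 |
| 0.010 | 0.01 | 20.4 | 20.4 |
| 0.010 | 0.02 | 19.6 | 39.3 |

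Allowing for earlier events lowers the counts only slightly. All values of r and e are assumptions.

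**5. Follow-up horizon**

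Section 2.5.4.1 runs 8 years from enrolment. In Section 2.6 the 8 years start either at the end of the 16-week intervention (about 4 months later) or at the last follow-up visit (about 4 + 8 = 12 months later). The sections disagree on either reading, by about 4 or about 12 months.

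**The case against.** The strongest counter-argument is about weight. DFS is exploratory. The sample size in Section 2.8 and the mixed models in Section 2.9 do not involve it, and no DFS hypothesis or power is stated. That stands and limits the importance of the point.

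It could also be said that a journal article condenses a fuller protocol. That would excuse a missing censoring rule, but not this: the article sets out a complete list for DFS and names death explicitly in the three neighbouring definitions.

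Several stronger readings are tempting but go beyond the document:

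- **That women who die are censored for DFS, or kept at risk after death.** No censoring or competing-risk rule is given. The text shows only that these deaths are not DFS events. Censoring at death would in any case take a woman out of the risk set; the problem would then be a competing event handled as censoring.
- **That the endpoint is meaningless.** Without death it is a time to recurrence or new cancer. It is mislabelled, but interpretable once the handling of death is stated.
- **That DFS will have fewer events than DDFS.** DFS also counts local and regional recurrence, contralateral cancer and in-situ disease. It would have fewer events only if uncounted deaths outnumbered women whose only events were of those types, and the document gives neither number.
- **That a large share of DFS events is lost, mainly cardiometabolic deaths.** No rates or causes of death are given. Table 1 excludes smokers and women whose cardiovascular disease, uncontrolled diabetes or hypertension precludes exercise.
- **That the two follow-up horizons are one year apart.** That is only one of two readings of Section 2.6.

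**Conclusion.** The point holds as an error in a stated endpoint definition. DFS omits death while OS and DDFS count all deaths and RFI counts breast cancer deaths, so the endpoints do not nest and DFS can exceed DDFS. This follows from the wording alone and needs no assumption about rates.

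The size does rest on assumptions: at 0.3% to 1.0% per year, about 6 to 21 deaths among 276 women over 8 years would go uncounted, or slightly fewer once earlier DFS events are allowed for. The consequence is confined to the exploratory long-term outcomes. The primary and secondary analyses and the sample size are unaffected.

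The mismatch in follow-up horizon is a separate, minor inconsistency and adds no weight to the DFS point.

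**What to change.** Either of two changes to Section 2.5.4.1 would resolve the point:

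1. Add death from any cause to the DFS event list. This costs one phrase and needs no new data, because deaths are already collected for OS.
2. Keep the present list, rename the endpoint as time to recurrence or new cancer, and state that death is treated as a competing event. This also needs no new data, but it changes the endpoint's name and requires a competing-risk analysis.

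Separately, state one follow-up horizon with one starting point in both Section 2.5.4.1 and Section 2.6. Both edits are best made before the long-term outcomes are analysed.
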